### 2.2. Study Participants

The inclusion criteria will be:Person who currently smokes ≥5 cigarettes per day [25] (conventional cigarette or equivalent in nicotine content from HTP or ENDS);Adult persons who smoke (≥18 years old);Ability and willingness to provide informed consent or presence of a legal representative who consents.

The exclusion criteria will be:Persons < 18 years old;Pregnant or breastfeeding women;Current or past use of pharmacological or behavioral smoking cessation supports [25];Concurrent dependence on alcohol or other substances of abuse (excluding nicotine) [25];Advanced neurocognitive degenerative disorders;Unstable psychiatric conditions (including active suicidal ideation, recent psychiatric hospitalization, and/or changes in psychiatric medication within the past 3 months) [26,27];Inability or refusal to provide informed consent;Inability to access the integrated telemedicine platform and/or use wearable remote-monitoring devices;Participants without access to home medical devices for monitoring cardiopulmonary parameters (blood pressure monitor and pulse oximeter), required to perform the scheduled home assessments.

No restrictions regarding gender, race, nicotine addiction, or motivation to quit smoking will be enforced.

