### 2.5. Outcomes and Data Collection

#### 2.5.1. Primary Outcome

The primary outcome of the study will be the effectiveness of the program on smoking cessation, assessed through Continuous Abstinence Rates (CARs) and Point Prevalence Abstinence (PPA).

CARs will be defined as sustained smoking abstinence throughout the follow-up period without relapse [28]. CARs will be calculated as the proportion of participants who maintain continuous smoking abstinence at the 6-month and 12-month follow-up assessments without relapse during the observation period.

PPA will be defined as abstinence from smoking at the time of assessment, regardless of any previous smoking relapses during follow-up [28]. PPA will be calculated as the proportion of participants reporting abstinence from smoking at the 6-month and 12-month follow-up assessments, regardless of previous smoking relapses during follow-up.

Both CARs and PPA will be assessed using self-reported smoking status collected through the smoker diary and will be computed 6 and 12 months after baseline [28]. Smoking abstinence outcomes will be assessed through self-reported smoking status, consistent with the telemedicine-based design of the Wear-Smile project.

No biochemical verification of smoking abstinence (e.g., exhaled carbon monoxide or cotinine testing) will be performed.

The timing at 6 and 12 months to assess smoking behavior status was established because a 6-month abstinence period was considered indicative of long-term smoking cessation, as it allows for a more reliable estimation of the proportion of participants who will maintain abstinence even in the subsequent years [8]. A permanent effect of smoking cessation treatment was estimated to be 50% of the Continuous Abstinence Rate at 6 months [8].

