Before performing inferential analyses, an Exploratory Data Analysis (EDA) will be conducted to describe the characteristics of the sample and to identify any anomalies or patterns in the data.

Continuous variables will be presented as mean and standard deviation (SD) for normally distributed data and as median and interquartile range (IQR) for non-normally distributed data. Categorical variables will be reported as frequencies and percentages. The Shapiro–Wilk test will be used to assess the normality of distributions and determine the appropriate use of parametric or non-parametric tests.

Longitudinal changes in primary and secondary outcomes over time (baseline, 6 months, and 12 months) will additionally be analyzed using mixed-effects regression models accounting for repeated measurements within participants.

Comparisons between the intervention group (telerehabilitation using the integrated telemedicine platform and wearable remote-monitoring devices) and the control group (standard multimodal behavioral-psychological treatment without telemedicine or wearable devices) will be performed using Student’s t-test for normally distributed continuous variables and the Mann–Whitney U test for non-normally distributed variables.

Within-group longitudinal comparisons across follow-up assessments will be performed using paired Student’s t-tests or Wilcoxon signed-rank tests, as appropriate according to data distribution.

Comparisons between categorical variables, including smoking cessation status (abstinent/non-abstinent), will be performed using the Chi-square test or Fisher’s exact test when appropriate.

Associations between the intervention and both primary and secondary outcomes will be explored using Pearson’s correlation coefficient for normally distributed variables and Spearman’s rank correlation coefficient for non-normally distributed variables.

To control for potential confounding factors (e.g., age, gender, comorbidities), multivariate linear regression models will be applied. In addition, multiple logistic regression will be used to identify predictors of successful smoking cessation. The dependent variable will be smoking cessation status (yes/no), and the independent variables will include type of nicotine use (combustible tobacco vs. HTP vs. ENDS), age, gender, motivation, dependence severity, and comorbidities.

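### 12-month CAR is nested in 6-month CAR and cannot rise between them, so the planned longitudinal-change model does not suit CAR

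*Protocol article*

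**What the plan says.** Section 2.5.1 of the protocol article defines the first primary measure as follows: "CARs will be defined as sustained smoking abstinence throughout the follow-up period without relapse". It is calculated as the proportion of participants who "maintain continuous smoking abstinence at the 6-month and 12-month follow-up assessments without relapse during the observation period". Both CAR and PPA "will be computed 6 and 12 months after baseline", so both CAR windows start at baseline.

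The second primary measure is different: "PPA will be defined as abstinence from smoking at the time of assessment, regardless of any previous smoking relapses during follow-up".

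Section 2.6 then plans, for the primary outcomes as a class: "Longitudinal changes in primary and secondary outcomes over time (baseline, 6 months, and 12 months) will additionally be analyzed using mixed-effects regression models". The same section says: "Within-group longitudinal comparisons across follow-up assessments will be performed using paired Student’s t-tests or Wilcoxon signed-rank tests". For abstinence status it also gives: "Comparisons between categorical variables, including smoking cessation status (abstinent/non-abstinent), will be performed using the Chi-square test or Fisher’s exact test when appropriate".

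Baseline is one of the modelled time points, and Table 1 marks CAR at time 0. Yet the first inclusion criterion in Section 2.2 is "Person who currently smokes ≥5 cigarettes per day" (or the nicotine equivalent from heated or electronic products), so nobody is abstinent at entry.

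**The concern.** A longitudinal-change model asks whether an outcome moved between visits and whether it moved differently by arm. That makes sense for an outcome that is measured afresh at each visit and can move either way. CAR is cumulative. A participant who meets it at 12 months must have met it at 6 months, so the only possible change between those visits is from success to failure. The hypothesis of no change from 6 to 12 months is then true only if nobody relapses.

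The arm-by-time term is the part most likely to be read as a treatment finding, as evidence that an effect fades or lasts. For CAR it depends both on how likely abstainers are to relapse and on how many abstainers each arm had at 6 months. A programme that produced more quitters could appear to lose ground faster with no difference in relapse risk. Removing the baseline time point would not cure this, because the nesting lies between 6 and 12 months.

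**Working it through.** **Nesting.** CAR at 6 months requires no relapse in months 0-6, and CAR at 12 months requires none in months 0-12. The second set lies inside the first. For each participant and each arm, CAR12 ≤ CAR6.

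**Baseline.** All participants smoke at entry, so CAR at time 0 is 0 in both arms, or undefined because no follow-up has elapsed.

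**Inputs.** The article gives no abstinence or relapse rates, so the rates below are assumptions. The sample size of 51 per arm is the plan's own figure. It is reproduced by a one-sided two-sample t-test with a standardised difference of 0.5 (assumed for the stated medium effect), α = 0.05 and power 0.80, which gives 50.15, rounded up to 51 per arm and 102 in total. The point does not depend on it.

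**Formulas.** Let p6 be 6-month CAR, and r the share of 6-month continuous abstainers still abstinent at 12 months. E denotes the experimental group (EG) and C the control group (CG).
- 12-month CAR: p12 = p6 × r
- absolute fall: p6 × (1 − r)
- logit fall: logit(p6) − logit(p6 × r)
- relative fall: 1 − r

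Example with p6 = 0.30 (EG) and 0.15 (CG), r = 0.5 in both:
- EG: 0.30 × 0.5 = 15.0 points; logit(0.30) − logit(0.15) = −0.847 + 1.735 = 0.89
- CG: 0.15 × 0.5 = 7.5 points; logit(0.15) − logit(0.075) = −1.735 + 2.512 = 0.78

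Further cases with the same 6-month rates:

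| Retention EG / CG | Absolute fall, points (EG v CG) | Logit fall (EG v CG) | Relative fall (EG v CG) |
|---|---|---|---|
| 0.5 / 0.5 | 15.0 v 7.5 | 0.89 v 0.78 | 50% v 50% |
| 0.7 / 0.7 | 9.0 v 4.5 | 0.48 v 0.41 | 30% v 30% |
| 0.7 / 0.5 | 9.0 v 7.5 | 0.48 v 0.78 | 30% v 50% |
| 0.75 / 0.5 | 7.5 v 7.5 | 0.39 v 0.78 | 25% v 50% |
| 0.8 / 0.5 | 6.0 v 7.5 | 0.31 v 0.78 | 20% v 50% |
| 0.9 / 0.5 | 3.0 v 7.5 | 0.15 v 0.78 | 10% v 50% |

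**What the table shows.** With identical relapse risk (first two rows), the absolute arm-by-time contrast is not zero: 7.5 and 4.5 points. With relapse risk halved in the EG (25% v 50%), the same contrast is exactly zero. On the absolute scale the interaction therefore does not measure a difference in relapse.

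The absolute falls tie at rE = 1 − (pC/pE)(1 − rC) = 1 − (0.15/0.30)(0.5) = 0.75. Above that retention the arm with more quitters falls less. On the logit scale the tie comes earlier:
- the CG odds shrink by the factor (0.075/0.925) ÷ (0.15/0.85) = 0.459
- the EG odds become (0.30/0.70) × 0.459 = 0.197, so p12 = 0.197/1.197 = 0.1645
- rE = 0.1645/0.30 ≈ 0.55

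**Sampling variation.** A binomial simulation used 51 per arm, 6-month rates of 30% and 15%, and CG retention of 0.5. The EG showed the larger absolute fall in 86% of trials at EG retention 0.5, 54% at 0.7, 42% at 0.75, 31% at 0.8 and 10% at 0.9.

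**The case against.** **The model is additional.** This stands. The arms are also compared on abstinence status by Chi-square or Fisher's exact test, and nesting does not affect that comparison at either visit. From baseline to either follow-up, the arm with more continuous abstainers shows the larger gain (30 v 15 points at 6 months in the example), so the whole fitted trajectory need not contradict the main result.

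**A reader might infer that the arm with more quitters must show the larger decline by construction.** The documents do not support this. Only the direction is fixed. The size depends on retention in each arm, and the table shows the order reversing. Even with equal retention the relative declines are the same.

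**A reader might also infer that the EG would often show a significant within-arm deterioration while the CG looks stable.** Assume 17/51 and 8/51 abstinent at 6 months and 40% relapse in both arms. An exact McNemar test is then significant with 6 relapses (2 × 0.5^6 = 0.031), which has probability 74% in the EG and 5% in the CG. But the plan does not name that test. The paired-test sentence in Section 2.6 does not mention CAR and suits measured variables. The figures also leave out the planned Bonferroni correction. With three time contrasts (an assumption), 7 relapses are needed and the probabilities fall to 55% and 1%. At the same rates the logit declines are 0.69 and 0.58. That contrast of about 0.1 is small for 51 per arm.

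**Model form may be left to an analysis plan.** Scale and coding may be. But the article itself fixes the outcomes and the time points, and it includes CAR.

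**Conclusion.** The concern holds in a limited form. As written, Section 2.6 applies a change-over-time model to an outcome that is 0 or undefined at baseline and can only stay level or fall from 6 to 12 months. For CAR, the 6-to-12-month time effect is fixed in direction, and the arm-by-time term mixes relapse risk with the number at risk of relapse. If relapse risk is equal, the arm with more 6-month abstainers has the larger expected decline on the absolute and logit scales and the same relative decline. If that arm keeps its quitters sufficiently better, the pattern reverses: above 75% v 50% retention on the absolute scale, and about 55% v 50% on the logit scale, at 6-month rates of 30% and 15%.

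The nesting follows from the definitions alone. Every size quoted rests on assumed rates. Nothing in the article says that a fall in CAR would be read as harm. Severity is low, because the model supplements the between-arm test and leaves it intact.

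**What to change.** In Section 2.6:
- Exclude CAR from the longitudinal-change model, and state that the within-group paired tests do not apply to it.
- Compare CAR between arms separately at 6 and at 12 months.
- Keep longitudinal modelling for PPA and the other repeated outcomes. PPA is also 0 at baseline, so its informative contrast over time is 6 v 12 months, where it can move either way.
- If durability is of interest, report descriptively by arm the proportion of 6-month continuous abstainers still abstinent at 12 months.

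This costs about a sentence of wording and no new data. Section 2.7 says that enrolment has not started, so the change can be made before any participant is recruited.

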Participants will be randomly distributed equally (in a 1:1 ratio) into the experimental group (EG) and control group (CG). The random allocation sequence will be carried out by the web-based randomization service Research Randomizer (freely accessible online at: https://www.randomizer.org/, accessed on 26 May 2026) by an independent researcher not involved in participant recruitment, eligibility evaluation, or outcome assessment. Allocation concealment will be ensured using sequentially numbered, opaque, sealed envelopes prepared by the independent researcher. The envelopes will be opened sequentially only after the participant has completed the baseline assessment and has been formally enrolled in the study, thereby preventing foreknowledge of treatment allocation and minimizing selection bias.

Due to the nature of the intervention, participants and healthcare providers cannot be blinded to group allocation. Outcome measures will be collected using standardized assessment procedures to minimize assessment bias by independent researchers not involved in participant recruitment, eligibility evaluation, or randomization allocation.

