### 2.6. Statistical Analysis

An a priori sample size estimation was performed using G*Power software version 3.1.9.7 [36]. The calculation was based on the primary outcome (CAR), assuming a one-tailed test, a type I error (α) of 0.05, a statistical power (1−β) of 0.80, and a medium expected effect size. Based on these assumptions, the estimated sample size is 102 participants (51 per group).

The data collected will be pseudonymized (a technique that modifies and masks personal and sensitive data of a natural person to prevent direct or easy attribution to the individual) and will be used exclusively for the purposes of the Wear-Smile study project.

Statistical analyses will be performed according to the intention-to-treat (ITT) principle. Per-protocol analyses will additionally be conducted as sensitivity analyses.

The statistical analysis will be applied to analyze continuous and categorical variables, with particular attention to the handling of missing data and the analysis of both intra- and inter-subject variability.

To enhance data interpretation and understanding of distributions, graphical representations such as histograms, boxplots conditioned on the target variable, and scatter plots will be employed.

To minimize the risk of bias due to missing data, a missing data analysis will be performed to assess whether data are Missing Completely at Random (MCAR) or dependent on other variables. If missing data exceeds 5%, it will be handled using multiple imputation techniques based on appropriate statistical models, thereby reducing the risk of bias.

The adoption of these methodologies will strengthen the scientific evidence regarding the effectiveness of telerehabilitation for smoking cessation, optimize result interpretation, and provide valuable insights for future clinical implementations and public health policies.

A sensitivity analysis will be conducted to compare results between the original datasets and the imputed datasets.

Statistical analyses will be performed using SPSS version 28.0, R version 4.2, or STATA version 17.0. The level of statistical significance will be set at *p* < 0.05 for all tests, with Bonferroni correction applied for multiple comparisons to control the risk of Type I error. Effect sizes and 95% confidence intervals (95% CI) will also be reported whenever appropriate.

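### If Fisher's exact test is the small-count fallback for abstinence, Boschloo's test in its place would gain power at very low quit rates: an optional improvement, not an error

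*Protocol article*

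**What the plan says.** Section 2.6 states that comparisons of categorical variables, "including smoking cessation status (abstinent/non-abstinent), will be performed using the Chi-square test or Fisher’s exact test when appropriate". It does not define the condition for using Fisher's test, and it does not say whether the test is one- or two-sided.

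The binary outcome most likely to give small counts is continuous abstinence (CAR). Section 2.5.1 defines it strictly: "CARs will be calculated as the proportion of participants who maintain continuous smoking abstinence at the 6-month and 12-month follow-up assessments without relapse". Point prevalence abstinence (PPA) is reported alongside it, both at 6 and 12 months.

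The sample size in Section 2.6 is 51 per group. It rests on CAR, a one-tailed 0.05 level, 80% power and "a medium expected effect size". No abstinence rate is given for either arm. Section 2.6 adds: "The level of statistical significance will be set at *p* < 0.05 for all tests, with Bonferroni correction applied for multiple comparisons". The number of comparisons that share the correction is not stated.

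**The concern.** Fisher's test treats the total number of abstainers as fixed. Here only the arm sizes are fixed, by 1:1 randomisation (Section 2.1), and the total is random. With few abstainers the conditional distribution has few possible values, so the test's actual error rate falls far below its nominal level and power is lost. Boschloo's test uses Fisher's p-value as its statistic but computes its probability with only the arm sizes fixed. Its p-value is therefore never larger than Fisher's.

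This is the test for the primary outcome in a small trial. If continuous abstinence is rare, a real difference could be missed through the choice of fallback alone.

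**Working it through.** **Inputs.** From the article: 51 per arm; Chi-square or Fisher; level 0.05 with Bonferroni. Assumed, because the article is silent: Fisher is used when any expected count is below 5; Chi-square is uncorrected; tests are two-sided; outcome data are complete; and all abstinence rates.

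**The plan's own figure.** A two-sample t-test with d = 0.5, one-tailed 0.05, has power 0.806 at 51 per group, which matches the stated 102. For a proportion, Cohen's h = 0.5 gives 2 × (1.645 + 0.842)² / 0.5² = 49.5, so 50 per group. Neither calculation implies a particular pair of abstinence rates, so the stated N does not show whether the Fisher branch would be reached.

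**Trigger.** With equal arms the expected number of abstainers per arm is T/2, where T is the total. T/2 < 5 means T ≤ 9.

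**Method.** All 52 × 52 outcome tables were enumerated. Boschloo's p-value is the maximum, over the common abstinence rate, of the probability of a Fisher p-value at least as small as the one observed. Power is the sum of Bin(x; 51, p₁) × Bin(y; 51, p₀) over rejected tables.

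**Which tables change at 0.05.** Within the Fisher branch only two splits change verdict, in either direction:
- 5 v 0: Fisher p = 2 × (51·50·49·48·47)/(102·101·100·99·98) = 0.056; Boschloo p = 0.037.
- 7 v 1: Fisher p = 0.060; Boschloo p = 0.038.

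No table rejected under the planned rule is lost.

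**Power at two-sided 0.05** (gains from unrounded values):

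| Control v experimental | Fisher branch used | Planned rule | Boschloo as fallback | Gain (points) |
|---|---|---|---|---|
| 1% v 9% | 97% | 21.8% | 35.3% | 13.5 |
| 2% v 12% | 83% | 36.2% | 47.6% | 11.4 |
| 2% v 15% | 63% | 58.3% | 67.7% | 9.4 |
| 3% v 15% | 56% | 50.1% | 57.4% | 7.3 |
| 5% v 15% | 42% | 35.1% | 38.9% | 3.8 |
| 5% v 20% | 16% | 63.8% | 65.5% | 1.8 |
| 10% v 25% | 1% | 51.8% | 51.8% | under 0.1 |

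Check on the 2% v 12% row: P(5 v 0) = 0.0583 and P(7 v 1) = 0.0556, which sum to 0.114, the whole gain.

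**One-sided 0.05.** 2% v 12%: 48.2% to 59.1%. 5% v 15%: 44.2% to 47.3%. 10% v 25%: 64.4% for both.

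**Bonferroni.** The number of comparisons is not stated, so two levels are shown, both two-sided.
- 0.025 (for example CAR and PPA): 2% v 12% goes from 22.2% to 32.4%, and 2% v 15% from 41.9% to 52.4%. The gain is about 10 points in each case.
- 0.0125 (CAR and PPA at two times): 2% v 12% goes from 15.9% to 21.2%, about 5 points; 5% v 15% gains about 1 point.

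At these stricter levels 5 v 0 and 7 v 1 are non-significant under both tests, and other splits carry the gain.

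**Error rate at nominal two-sided 0.05.** At a common rate of 5%, the planned rule rejects in 0.9% of trials and the modified rule in 2.3%. The maximum over all common rates is 5.9% for both, and it arises in the Chi-square branch.

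**The case against.** Chi-square with Fisher as alternative is a standard and valid pairing. Fisher's test never exceeds its level, and nothing in the article is misstated or contradicted. That stands: the point concerns efficiency only.

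The trigger and the rates are not the article's. A reader might infer that the plan loses about 11 points of power. The documents do not support that. The figure needs a control rate near 2%, roughly one quitter among 51 people receiving in-person multidisciplinary care, and an unadjusted 0.05. It is neither typical (5% v 15% gains 4 points) nor a ceiling (1% v 9% gains 13.5). Low continuous abstinence is conceivable because no relapse is allowed, but the article states no rate. The benefit also shrinks at 0.0125, and few splits change verdict. All of this stands and limits the size of the point.

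A reader might also infer that an unconditional test should replace the whole rule. That is not always a gain: at 5% v 20%, two-sided, the planned rule has 63.8% power and Boschloo on every table 59.4%, partly because the uncorrected Chi-square test can exceed its level.

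Finally, Boschloo's own error guarantee applies when it is used on every table. As a fallback it neither repairs nor worsens the 5.9% maximum. That also stands, and the fix should not be presented as better error control.

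**Conclusion.** The point holds as an optional efficiency improvement, conditional on Fisher's test being triggered by an expected count below 5. Replacing only that branch cannot lower power and does not raise the rule's maximum error rate at 0.05.

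The gain is material only if control abstinence is very low: about 7 to 11 points at 2% to 3% control, 2 to 4 points at 5%, and nil from about 10%, at two-sided 0.05 before multiplicity correction. At 2% v 12% it is about 10 points at 0.025 and 5 at 0.0125. All of the rates are assumptions. The documents do not support calling Fisher's test an error.

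**What to change.** In the Section 2.6 sentence on categorical comparisons, name Boschloo's unconditional exact test in place of Fisher's and state the trigger. For example: abstinence will be compared with the Chi-square test, or with Boschloo's exact test if any expected count is below 5, at the significance level that applies after the multiplicity correction. State also that the Chi-square branch is unchanged.

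The cost is a few words and software with an unconditional exact test; R is already one of the listed packages. No extra participants are needed, and enrolment has not started (Section 2.7), so the choice can be pre-specified. One limit remains: like Fisher's, Boschloo's p-values do not pool directly across multiply imputed datasets, so this change does not settle the imputed analysis that Section 2.6 plans when more than 5% of data are missing.

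### The logistic model for predictors of cessation has at least seven slopes but at most 7.3 events per slope with 102 participants, so ordinary fitting risks moderate inflation and, with few HTP or ENDS quitters, separation

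*Protocol article*

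**What the plan says.** All of the following is in Section 2.6 of the protocol article unless noted.

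- **Model.** The protocol states that "multiple logistic regression will be used to identify predictors of successful smoking cessation". The outcome is cessation, yes or no. It is not said whether this is continuous or point prevalence abstinence, or whether it is taken at 6 or 12 months.
- **Covariates.** The list is fixed: "the independent variables will include type of nicotine use (combustible tobacco vs. HTP vs. ENDS), age, gender, motivation, dependence severity, and comorbidities". Study arm is not named in it. The closing paragraph on subgroups also puts product type into multivariable regression models as a possible confounder.
- **Sample size.** The total is 102, or 51 per group, sized on continuous abstinence "assuming a one-tailed test, a type I error (α) of 0.05, a statistical power (1−β) of 0.80, and a medium expected effect size".
- **Quit rate.** None is given. Section 2.5.1 defines the outcome ("CARs will be calculated as the proportion of participants who maintain continuous smoking abstinence at the 6-month and 12-month follow-up assessments") without an expected value.
- **Comparison between arms.** This is separate from the logistic model: comparisons of categorical variables, including cessation status, "will be performed using the Chi-square test or Fisher’s exact test when appropriate".

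Section 2.6 sets no limit on the number of parameters and mentions neither variable reduction nor penalisation.

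**The concern.** In logistic regression the information comes from the smaller outcome class, here probably the quitters, and not from the 102 enrolled. With few events per slope, ordinary maximum likelihood tends to push log odds ratios away from zero. If a product group contains no quitters, or only quitters, the data are separated and that group's odds ratio has no finite estimate. HTP and ENDS users are the most exposed if they are minorities of the sample.

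At stake is the stated purpose of the model, naming predictors of cessation, and the product-type contrast. The Discussion counts the inclusion of several product types as a strength of the trial.

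**Working it through.** **Step 1. The plan's own figure.** With a one-tailed α of 0.05, power of 0.80 and "medium" read as a standardised difference of 0.5, the normal approximation gives 2 × (1.645 + 0.842)² / 0.5² = 49.5, so 50 per group. The noncentral-t calculation gives 51 per group (power 0.806), so 102. The stated size is reproduced, but it carries no abstinence rate and so fixes no number of events.

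**Step 2. Number of slopes.** Product type 2, age 1, gender 1, motivation 1, dependence 1, comorbidities 1: 2 + 1 + 1 + 1 + 1 + 1 = 7 at minimum. Entering comorbidities separately, or adding study arm, raises this.

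**Step 3. Events per slope.** Events = 102 × quit rate, divided by 7. The quit rates are assumptions.

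| Quit rate | Events | Events per slope |
|---|---|---|
| 10% | 10.2 | 1.5 |
| 20% | 20.4 | 2.9 |
| 30% | 30.6 | 4.4 |
| 40% | 40.8 | 5.8 |
| 50% | 51.0 | 7.3 |

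Above 50% the non-quitters become the smaller class, so 51 / 7 = 7.3 is the ceiling at any rate.

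**Step 4. Is 10% to 30% reasonable?** Read "medium" as Cohen's h = 0.5. The experimental rate is then sin²(arcsin √p + 0.25) for control rate p, and events = 51 × (sum of the two rates).

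| Control rate | Experimental rate | Events |
|---|---|---|
| 5% | 21.0% | 13 |
| 10% | 29.3% | 20 |
| 15% | 36.4% | 26 |
| 20% | 42.8% | 32 |
| 30% | 54.4% | 43 |

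Ten to thirty quitters is plausible, but it is not a maximum.

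**Step 5. Separation.** Both simulations used 102 participants and seven slopes. Product mixes (combustible/HTP/ENDS) and true effects are assumptions. Simulation A used 1,000 runs per scenario, log odds ratios of +0.5 per SD for motivation and −0.5 per SD for dependence, and flagged separation when any slope exceeded 8 in absolute value. Simulation B used 2,000 runs, log odds ratios of 0.3 to 0.5 in absolute value, and also counted non-convergence.

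| Simulation, product mix | 10% | 15% | 20% | 30% quitting |
|---|---|---|---|---|
| A, 80/10/10 | 51% | 33% | 22% | 9% |
| A, 70/15/15 | 32% | 15% | 8% | 2% |
| A, 50/25/25 | 13% | 3% | 1% | 0% |
| B, 70/15/15 | 58% | 33% | 19% | 5% |
| B, 34/33/33 | 16% | 4% | 1% | 0% |

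The rates fall quickly as quitting rises and as the product mix evens out.

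**Step 6. Bias where the ordinary fit converged.** In A, a true log odds ratio of 0.5 averaged 0.55 to 0.61, an inflation of 10% to 22%. As odds ratios, exp(0.5) = 1.65 became exp(0.55) = 1.73 to exp(0.61) = 1.84. In B, the covariates other than product type were mostly 10% to 25% too large at about 10 to 30 events, with one cell at 37%. Product type behaved differently: at 70/15/15, its converged log odds ratios averaged 0.20 and 0.25 of the true value at 10% quitting, and 0.77 and 0.80 at 15%, because separated datasets drop out. In A, Firth's fit averaged 0.48 to 0.53 for a true 0.5 and was finite in every run.

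**The case against.** The strongest reply has four parts.

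1. **The bias is small against the noise.** A shift of 0.05 to 0.11 on the log scale compares with a standard error for motivation of about 0.26 to 0.36 at 10% to 30% quitting. Ordinary Wald 95% intervals among non-separated fits covered the truth in about 92% to 98% of runs. This stands. A reader might infer that the odds ratios are bound to be inflated or not estimable, but neither the document nor the simulations support that. Separation is a risk that can be close to nil, and product-type estimates can be biased towards zero.
2. **The number of quitters is not in the protocol.** This also stands. Ten to thirty is an assumption, and point prevalence abstinence could give more. The ceiling of 7.3 does not depend on it.
3. **The estimator and the coding belong in an analysis plan that is not shown.** This stands in part, because the protocol does not write "maximum likelihood" or say how scores are coded. But it does fix the method, the covariate list and the sample size, and these fit poorly together. Multiple logistic regression without further qualification means the ordinary fit.
4. **The consequence is limited.** A reader might infer that the trial's main result is compromised. It is not: the arms are compared by chi-square or Fisher's exact test. This is a separate analysis of predictors, and the authors call the trial's evidence preliminary.

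A further fair point is that Firth's method keeps all seven slopes. It makes product-type estimates finite, not informative. At 10% quitting the standard error for HTP was about 0.85 to 1.05, so the upper and lower 95% limits differ by a factor of exp(2 × 1.96 × 0.85) ≈ 28 to exp(2 × 1.96 × 1.05) ≈ 61.

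**Conclusion.** The point holds as a risk to one non-primary analysis, and the plan should be changed. That the model has at least seven slopes and at most 7.3 events per slope follows from the protocol alone. The 1.5 to 4.4 events per slope rest on an assumed 10% to 30% quit rate. The inflation of mostly 10% to 25% and the separation rates, from about 0% to about half of trials (58% in the least favourable case when non-convergence is counted), also rest on assumed effects and product mixes. The inflation applies to the covariates other than product type. Separation matters if HTP or ENDS groups are small and quitting is low. The comparison of abstinence between arms is not affected, and nothing here extends to the mixed-effects models in the same section.

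**What to change.** In Section 2.6, state that the multiple logistic regression for predictors of cessation will be fitted by Firth penalised likelihood, with profile penalised-likelihood 95% confidence intervals, in R or STATA (both already named). Enter age, motivation and dependence severity as continuous scores and comorbidities as a single term. Describe the predictor results as exploratory. Leave the mixed-effects models as they are, since ordinary Firth logistic regression does not cover them.

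**Cost.** Wording only: no added participants, visits or data, and Section 2.7 says that enrolment has not started. There are three downsides. Estimates are mildly shrunk. If multiple imputation is triggered (missing data above 5%), profile intervals are not pooled by the standard Rubin rules, so a pooling method suited to penalised fits must be named. Product-type intervals will be finite but still wide, and should be reported as such.
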